**Methods/Design:**

The purpose of this project is to compare the effectiveness of several approaches to influencing hearing protector use. Approaches include: a) an interactive, predictors-based intervention delivered via the Internet; b) a static informational web site; and c) a mailed sampler of hearing protectors. The goals are to further develop an intervention to promote farmers’ use of HPDs, and compare the effectiveness of the interventions delivered in various combinations. Participants will include 701 farmers. Sites will be affiliates of a major farmer organization. Data will be collected at baseline, 6, and 12 months. A random intercept mixed model will be used to explore the fixed effects of the three NIHL prevention interventions over time while adjusting for age and gender. This project will involve a partnership between the University of Michigan and a major farmer organization to accomplish project aims.

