### Analysis and sample size estimates

Power analysis was conducted using PASS software [43] to determine the sample size needed to provide 80% power to detect important effects that we expect to see in the research, based on comparisons between conditions with alpha of .05 two tailed, given findings from past studies. Given how low use of HPDs is among farmers, we expect to produce and detect changes of 13% in percent time use between conditions with a standard deviation of .3, thus an effect size d of .43 which is a bit smaller than what Cohen (1992) defined as medium sized. A sample size of 85 per group is needed to have 80% power to detect an effect size d = .43. With a second posttest at 12 months we have allowed for a loss of up to 40%, so will recruit 709 subjects total to retain 425 or 85 per group.

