### Data analysis plan

Descriptive statistics will determine frequency distributions, percentage distributions, and means and standard deviations. Distributions of variables will be examined to detect and correct values outside of the legal range. They will also be examined for the normality of their distribution and transformed as appropriate so they meet the assumptions of the statistical analysis. Cronbach’s alphas will be used to assess internal consistency of multiple item scales as a measure of reliability. Scales with alphas of at least .63 will be considered usable. The various experimental groups will be compared on baseline values of variables. Independent variables found to differ between groups at baseline will be added to the analyses as covariates.

A random intercept mixed model will be used to explore the fixed effects of the three NIHL prevention interventions over time adjusting for age and gender as covariates. The model will include a random intercept for subjects to control for non-independence of repeated measures. A compound symmetric covariance structure will be specified in the model. Each of the outcomes: use of HPDS, attitudes, and beliefs will be modeled separately in order to investigate the effects of web interventions and mailed hearing protection devices. The data will be analyzed within two research designs. First will be the complete factorial design 2 (interactive vs. static web) x 2 (sent HPDs) x 3 (times: baseline, 6 months, and 12 months). This will not include the condition in which participants are simply sent HPDs. The second design will include all conditions in an incomplete factorial 3 (interactive web vs, static web vs. no web) X (sent HPDs) x 3 (times: baseline, 6 months, 12 months). SAS 9.3 (SAS Institute Inc., Cary, NC, USA) and SPSS 22 will be used for all analyses. A p-value of < .05 will indicate statistical significance.

#### Tests of hypotheses 1 and 2

Participants receiving interactive Web interventions will have higher HPD use and more favorable use-related attitudes/beliefs than participants not receiving Interactive Web interventions;Participants receiving the mailed HPD Intervention will have higher HPD use and more positive use-related attitudes/beliefs than participants not receiving the mailed HPD Intervention.

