The dependent measures used for all the aims are quantitative variables: the individual’s percentage of time using HPDs, and relevant attitudes/beliefs, as outlined in Table 1. Either before or after transformation they will be normally distributed so will be analyzed by linear random intercept mixed models.

All analyses to test Hypotheses 1 and 2 will include baseline data collection and will focus on the tests of interactions of time with web format and with sending HPDs. Tests of these interactions with time will indicate whether changes over time are equivalent in different groups, for example whether participants exposed to the interactive web intervention increased use of HPDs more than participants exposed to the static web intervention. Follow-up analyses will present mean use and mean scores on attitudes/beliefs by time and condition as estimated by the mixed model. The same analysis focusing on different interactions with time will be conducted to test hypothesis 2. Naturally, they will test the interactions of time with provision of HPDs to test the hypothesis that provision of HPDs will increase use and improve use-related attitudes/beliefs.

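### The mixed model imposes one variance and one correlation on baseline, 6 and 12 months with no robust standard error, which can distort the 12-month change and, under the allowed loss, the time-interaction tests

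*Protocol article*

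**What the plan says.** The abstract (Methods/Design) and the Data analysis plan both name a random intercept mixed model. The Data analysis plan then gives two consecutive sentences: "The model will include a random intercept for subjects to control for non-independence of repeated measures" and "A compound symmetric covariance structure will be specified in the model". Under the tests of Hypotheses 1 and 2 it repeats that the outcomes, transformed if necessary, are approximately normal, "so will be analyzed by linear random intercept mixed models". The test of Hypothesis 4 uses the same kind of model.

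The visits are fixed: "Data will be collected at baseline, 6, and 12 months". The tests of Hypotheses 1 and 2 "will focus on the tests of interactions of time with web format and with sending HPDs". Hypothesis 4 is a three-way interaction that includes time. With three visits, each of these tests has 2 degrees of freedom when web format has two levels.

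Under Analysis and sample size estimates the plan says "we have allowed for a loss of up to 40" per cent. No other covariance structure and no robust standard error is named, and no within-subject correlation is given anywhere.

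**The concern.** Whichever way the two sentences are read, the fitted covariance has two parameters: one variance for all visits, and one correlation for the pairs 0-6, 6-12 and 0-12 months. Two features of this trial make that restriction doubtful.

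- Measurements further apart often correlate less.
- HPD use is bounded at 0-100, and Table 2 reports 43.2% with zero use. If an intervention moves some non-users and not others, the spread at follow-up may change.

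With heavy loss, a likelihood analysis also relies on the assumed covariance to carry information from observed to missing visits. A wrong structure can then affect the estimated means as well as their standard errors. Hypotheses 1, 2 and 4 are all judged on change over time in this model, and the means by time and condition will be reported from it. Hypothesis 3 is left out here because the plan leaves its method open.

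**Working it through.** **1. Sample size.** The plan expects "changes of 13% in percent time use between conditions with a standard deviation of .3, thus an effect size d of .43", "based on comparisons between conditions with alpha of .05 two tailed".
- n = 2(1.96 + 0.8416)² / 0.43² = 84.9, so 85 per group.
- 425 / (1 - 0.40) = 708.3, so 709.

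Both of the plan's figures reproduce. Neither uses a within-subject correlation, so the covariance structure does not affect them.

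**2. Redundancy.** Let the random-intercept variance be b, the compound-symmetry covariance c and the residual variance s. The marginal covariance is V = (b + c)J + sI, where J is the matrix of ones, so only b + c is identified. With total variance 1 and correlation 0.5, the splits (b, c) = (0.5, 0), (0.3, 0.2) and (0, 0.5) give the same V. They also give the same standard error for the between-group 12-month change: 0.30 × √[(2/85) × 2 × (1 - 0.5)] = 0.0460. The redundancy changes no inference.

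**3. The 12-month change, complete data, equal variances.** Compound symmetry replaces each correlation by the mean r̄ of the three.
- Model SE / true SE = √[(1 - r̄) / (1 - r(0,12))].
- Type I error = 2[1 - Φ(1.96 × ratio)].

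All correlations below are assumptions.

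| r(0,6) / r(6,12) / r(0,12) | r̄ | SE ratio | Type I error |
|---|---|---|---|
| .5 / .5 / .5 | .500 | 1.00 | 5.0% |
| .6 / .6 / .5 | .567 | 0.93 | 6.8% |
| .5 / .65 / .4 | .517 | 0.90 | 7.9% |
| .6 / .7 / .45 | .583 | 0.87 | 8.8% |
| .7 / .7 / .5 | .633 | 0.86 | 9.3% |
| .7 / .7 / .49 | .630 | 0.85 | 9.5% |
| .5 / .5 / .6 | .533 | 1.08 | 3.4% |

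For .7/.7/.5 the 6-month change errs the other way: √[(1 - .633)/(1 - .7)] = 1.11, type I error 3.0%.

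**4. The planned 2-df test, complete data.** The statistic behaves as λ₁χ²₁ + λ₂χ²₁, referred to 5.991. For .7/.7/.5 the two orthogonal time contrasts have variances 0.500 and 0.233, and the model uses their average, 0.367. Hence λ = 1.364 and 0.636, which sum to 2, and the size is 5.5%. The errors in the two directions largely cancel. Across the assumed correlations the size is 5.0% to 5.5%.

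**5. The 2-df test with loss.** The compound-symmetric model was simulated by REML under no true effect. There were about 280 participants per factor level (709 × 4/5 ÷ 2 = 284) and 1,500 to 2,000 replicates. Dropout mechanisms and SDs are assumptions.
- Random loss of 40%, equal variances: about 6%.
- Loss depending on earlier observed values by the same rule in both arms, 42% to 46% missing at 12 months: 5.7% to 6.2%. Bias in the 12-month change was at most 0.003 SD.
- Random loss of 40%, .7/.7/.5, SDs rising as 1 / 1.15 / 1.3: 8.4% in simulation (Monte Carlo error about 0.7 points), with 12.0% for the 12-month change. A large-sample calculation compared the model covariance A⁻¹ with the true A⁻¹MA⁻¹, where A = ΣpW and M = ΣpWVW over the dropout patterns. It gives 6.5% to 7.0% when 40% are missing at 12 months through monotone dropout, depending on when the loss occurs. Hence about 7% to 8%.
- About 40% loss after 6 months, driven by the observed 6-month value in opposite directions in the two arms (deliberately severe), equal variances: 8.7% with bias 0.05 SD for .6/.7/.45, and 11.4% with bias 0.08 SD for .5/.65/.4. If the covariance truly is compound symmetric, the same dropout gives 5.2% and no material bias.

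At SD 0.30, those biases are 0.05 × 30 = 1.5 and 0.08 × 30 = 2.4 percentage points, against a planned difference of 13. The size depends on the dropout rule. A logistic rule with log-odds -0.5 ± the standardised 6-month value (40% missing) gives 10.9% and 14.1%, with biases of 0.07 and 0.09 SD.

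**The case against.** The case against is strong on several counts, and most of it stands.

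- A reader might infer that the model is over-parameterised and cannot be fitted. The text does not support that. It names one random intercept model throughout and never says that compound symmetry is a second, residual structure. Even if both were coded, step 2 shows that nothing in the inference changes.
- A reader might also infer that the 12-month standard errors are wrong. That does not follow either. They are correct if the correlations and variances are equal, too small in some cases and too large in others, and the document gives no values to decide between them.
- The 7% to 10% concerns a single 12-month contrast, which the plan does not name as a test. It does not rank 12 months above 6 months. The planned tests have 2 degrees of freedom and are much better protected.
- Covariance fallbacks and degrees-of-freedom methods are often left to a fuller plan. That covers what is absent here, but compound symmetry itself is a choice the article states.
- The plan will transform outcomes to meet model assumptions. This may steady the variance, but it does not make correlations equal, and a mass of zeros remains a mass of values at one point under any transformation.

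What the objection does not remove is the combination of heavy loss with rising variance or arm-dependent dropout. There the 2-df tests lose their protection, and in the arm-dependent case the true compound-symmetric comparison shows that the misspecified covariance, not the dropout alone, is the cause.

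**Conclusion.** The concern holds in a conditional form. Naming both a random intercept and compound symmetry is a wording matter. The restriction to one variance and one correlation, without robust standard errors, is a real and avoidable assumption.

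Its size rests on assumed correlations, SDs and dropout:
- For the 12-month change with complete data and equal variances, type I error is about 7% to 10% if the 0-12 month correlation is below average, and below 5% if it is above.
- For the planned tests of Hypotheses 1, 2 and 4, type I error is near 5% to 7% in the benign settings and about 7% to 8% with 40% random loss, declining correlations and rising variances. It is higher, with biased means, if dropout also depends on earlier use differently by arm. That last setting is deliberately severe and is not a prediction.

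The sample size is unaffected. The change is worth making because it is cheap and removes an untested assumption, not because an error has been shown.

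**What to change.** Replace the two covariance sentences in the Data analysis plan by wording such as: *The within-subject covariance over baseline, 6 and 12 months will be unstructured, without a separate random intercept, with Kenward-Roger degrees of freedom. If this model does not converge, a heterogeneous structure with robust (sandwich) standard errors will be used.* The fallback repairs the standard errors but does not by itself protect the means under dropout, so its use should be reported.

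To avoid a new contradiction, change the random intercept wording to match in the abstract, in the opening sentence of the model description in the Data analysis plan, under the tests of Hypotheses 1 and 2, and under the test of Hypothesis 4.

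The cost is six covariance parameters in place of two, which is negligible with about 700 participants, and a wording change. Recruitment, visits and sample size stay as they are.

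### H1 and H2 are each judged at p < .05 on several outcomes in two overlapping designs, and the plan does not say which outcome, design or contrast decides them

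*Protocol article*

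**What the plan says.** All of this is in the Protocol article.

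- **Threshold.** The Data analysis plan gives one rule for all analyses: "A p-value of < .05 will indicate statistical significance".
- **Two designs.** "The data will be analyzed within two research designs". The first is the complete 2x2 (interactive or static web, HPDs sent or not) over three times, without Group 5. For the other: "The second design will include all conditions in an incomplete factorial 3 (interactive web vs, static web vs. no web) X (sent HPDs"), again over three times.
- **Outcomes.** HPD use, attitudes and beliefs each get their own model. Table 2 lists HPD use and seven attitude/belief scales. The list under Outcome measures gives HPD use and four constructs, or six if interpersonal influences is split into its three subscales, and leaves out benefits. The text under Tests of hypotheses 1 and 2 refers to Table 1 for the outcomes, but Table 1 lists the study conditions.
- **Hypotheses.** H1 expects higher HPD use and "more favorable use-related attitudes/beliefs than participants not receiving Interactive Web interventions". H2 has the same form for mailed HPDs.
- **Tests.** H1 and H2 are tested through interactions of time with web format and with sending HPDs. The example given compares interactive with static web. Only H4 is tied to one design, the 2x2.
- **Power.** The sample size rests on percent time of HPD use alone, for "comparisons between conditions with alpha of .05 two tailed". HPD use is not called primary.

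**The concern.** Each hypothesis joins one behavioural outcome with a set of scales, and each outcome can be tested in either of two designs. The plan does not say what result counts as support. With every test judged at .05, one favourable scale could be reported as support, and the two designs could give different answers with no rule for choosing between them.

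The comparison for H1 is also not settled. As worded, it sets Groups 1 and 2 against Groups 3, 4 and 5; as illustrated, it sets interactive against static web. These are different contrasts with different comparators. The five-arm design adds a further problem: Table 1 has no group with neither web nor HPDs, so one of its six cells is empty.

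The trial sets out to find the most effective approach, so the claim for each intervention should rest on a test fixed in advance.

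**Working it through.** **1. The plan's own figure.** Inputs from Analysis and sample size estimates: "we expect to produce and detect changes of 13% in percent time use between conditions with a standard deviation of .3", two-sided alpha .05, 80% power, 40% loss.
- d = 0.13/0.30 = 0.433, given as .43.
- n per group = 2(1.960 + 0.842)²/0.43² = 15.70/0.1849 = 84.9, so 85. This matches "A sample size of 85 per group is needed to have 80% power to detect an effect size d = .43".
- 5 x 85 = 425, and 425/0.6 = 708.3, so 709. Reproduced.

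This calculation has one outcome, one two-group comparison and the whole .05.

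**2. False-positive chance.** With m independent tests at .05, the chance of at least one false positive is 1 − .95^m. For correlated outcomes it was simulated with equicorrelated outcomes and two independent contrasts. The outcome correlation is not in the documents, so a range is shown.

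| Outcomes | Scope, one design | Independent | r = .3 | r = .5 |
|---|---|---|---|---|
| 8 (Table 2) | one hypothesis, 8 tests | 34% | 30% | 25% |
| 8 (Table 2) | H1 and H2, 16 tests | 56% | 51% | 44% |
| 7 (text list, subscales split) | one hypothesis, 7 tests | 30% | 27% | 23% |
| 7 (text list, subscales split) | H1 and H2, 14 tests | 51% | 47% | 41% |
| 5 (text list) | one hypothesis, 5 tests | 23% | 21% | 18% |
| 5 (text list) | H1 and H2, 10 tests | 40% | 37% | 33% |

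**3. What the second design adds.** Fit the five group means with an additive model (intercept, interactive, static, HPD). The least-squares weights on Groups 1 to 5 are:
- HPD effect: +½, −½, +½, −½, 0.
- Interactive minus static: +½, +½, −½, −½, 0.

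Group 5 has weight 0 in both, so these are the 2x2 contrasts again. The new information in the five arms is web against no web.

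**4. The empty cell.** A full 3x2 model has six parameters for five observed groups, so its rank is 5. The mean for neither web nor HPDs, and any marginal mean that uses it, cannot be estimated.

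**5. The comparisons taken literally.** Let h be the HPD effect and wi and ws the interactive and static effects, assumed additive, with equal groups.
- H1, Groups 1, 2 v 3, 4, 5: HPDs are held by 1/2 against 2/3 of participants, which adds h/2 − 2h/3 = −h/6. The comparator also mixes static web with no web.
- H2, Groups 1, 3, 5 v 2, 4: h + (wi + ws)/3 − (wi + ws)/2 = h − (wi + ws)/6.

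If h = wi = 13 and ws = 6.5 (illustrative), the shifts are −2.2 and −3.25 points. They apply only if the groups are pooled in this way.

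**6. Power of the deciding tests.** Each main effect in the 2x2 compares 170 with 170 (2 x 85). Assume a 13-point difference at both follow-ups, SD 30, and compound symmetry with within-person correlation ρ. The 2-df effect-by-time test has noncentrality 0.433² x (170/2) x (2/3)/(1 − ρ) = 10.64/(1 − ρ).

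| ρ (assumed) | alpha .05 | alpha .025 |
|---|---|---|
| 0 | 84% | 76% |
| .3 | 95% | 91% |
| .5 | 99% | 98% |

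**The case against.** **The planned analysis is not confounded.** A reader might infer from the hypothesis wording and the empty cell that the H1 and H2 estimates will be biased. The documents do not support that. The planned tests are factor-by-time interactions with web format and HPDs as separate factors, the example is interactive versus static, and steps 3 and 5 show that the shifts need a raw pooling of groups that no section specifies. The plan itself calls the second design incomplete and tests the web-by-HPD interaction only in the 2x2. This objection stands. What remains is a mismatch in wording and a five-arm model whose terms are not stated.

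**The number of tests can be overstated.** A reader might count 8 outcomes x 2 hypotheses x 2 designs = 32 chances of error. H1 and H2 are separate hypotheses, and the designs share Groups 1 to 4 and largely repeat the same contrasts. The second design is therefore not 16 further independent tests. This also stands.

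**The plan does not say that one significant scale suffices.** Each hypothesis joins use and attitudes with an and. That is true, but the plan does not require all outcomes to be significant either. The false-positive figures describe an any-of reading that the text leaves open.

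**A full analysis plan may settle this.** A condensed article can leave multiplicity control to it, and HPD use is the only powered outcome. Missing detail alone would be no finding. Here, however, the article itself sets one threshold for every separately modelled outcome in two designs, and ties H4 to a design but not H1 or H2.

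**Conclusion.** The point holds as a matter of decision rule and wording. H1 and H2 have no deciding outcome, design or contrast. Under the stated threshold the chance of at least one false positive in one design is 25% to 34% per hypothesis, and 44% to 56% over both, with eight outcomes and an assumed outcome correlation of .5 down to 0. Eight is a count from Table 2; the shorter list under Outcome measures lowers the figures but leaves the conclusion unchanged.

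H1 as worded and H1 as illustrated are different comparisons and must be reconciled. The five-arm design cannot support a full web-by-HPD model, nor a comparison of any intervention with nothing unless additivity is assumed. The complete 2x2 and additive contrasts in the five arms remain sound.

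**What to change.** - **Deciding test.** Name HPD use, the powered outcome, in the complete 2x2. H1 is interactive v static averaged over HPD provision (Groups 1, 2 v 3, 4). H2 is HPDs v no HPDs averaged over web format (Groups 1, 3 v 2, 4).
- **Wording.** Reword H1 and H2 to match these contrasts.
- **Other scales.** List the attitude/belief scales explicitly and label them secondary, either with Holm adjustment or without significance claims.
- **Five arms.** Fit a five-level condition and use it only for Group 1 v 5 and Group 3 v 5, that is, web added to HPDs. State that effects against no intervention are not estimable.
- **Optional.** Apply Holm across H1 and H2.

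The cost is analysis-plan wording, with no new data. Fewer secondary results will be nominally significant. If Holm is used, power at its first step (.025) is about 91% at within-person correlation .3 and 98% at .5. It falls to 76%, below the planned 80%, only in the limiting case of zero correlation.

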#### Test of hypothesis 3: participants visiting the Web site more frequently will have higher HPD use than those visiting less frequently

We will assess the number of times that each individual accesses the Website and test the effect of number of views (separately for the Interactive Web Intervention and Static Web Intervention). We suspect that people with more exposures to the Website will show more impact of it (for both the Interactive Web Intervention and Static Web Intervention). However we do not expect the number of visits to be great so do not expect to have power to detect these effects. The method of analysis will depend on the distribution of number of visits. If there is little variability in number of visits this will be treated as a dichotomous predictor variable. If more variable, it will be treated as a continuous predictor. Whether significant or not, results will provide evidence about how the Interactive and Static Web Interventions work.

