**Table 1 Tab1:** **Study Conditions**

**Group**	**Observation**	**Intervention**			**Observations**
		**Interactive web information**	**Static web information**	**HPDs**	
1	Pretest	X		X	Post-tests at 6 & 12 months
2	Pretest	X			Post-tests at 6 & 12 months
3	Pretest		X	X	Post-tests at 6 & 12 months
4	Pretest		X		Post-tests at 6 & 12 months
5	Pretest			X	Post-tests at 6 & 12 months

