### Interventions

The study compares five prospective parallel groups receiving three distinct interventions, delivered in various combinations (Table 1). Participants in Groups 1 and 3 will be offered (Interactive or Static) Web-based information and, following verification of completion, a sampler of HPDs will be supplied to them. Participants in Groups 2 and 4 will be offered (Interactive or static) Web-based information and asked to verify completion. Participants in Group 5 will simply receive a sampler of HPDs on completion of the pretest.

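### The Hypothesis 3 visits test mixes web exposure with sampler receipt, because in Groups 1 and 3 the hearing protectors are sent only after verified web completion

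*Protocol article*

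**What the plan says.** The section on Hypothesis 3 proposes that people who visit the web site more often will use HPDs more. It counts each person's visits and will "test the effect of number of views (separately for the Interactive Web Intervention and Static Web Intervention"). Web format is the only split named. On the form of the predictor it says: "If there is little variability in number of visits this will be treated as a dichotomous predictor variable"; otherwise visits are continuous. No cut-point is given. The section does not anticipate adequate power, but says the result will inform how the two web interventions work, whether or not it reaches significance.

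The Interventions section sets when the sampler is sent. Participants in Groups 1 and 3 are offered the web information and, "following verification of completion, a sampler of HPDs will be supplied to them". Groups 2 and 4 get the web information and no sampler. Group 5 gets the sampler after the pretest, with no web condition attached.

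Under Hypothesis 2 the protocol expects the sampler to raise HPD use.

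**The concern.** Hypothesis 3 asks about web dose. In half of each pooled analysis set, however, completing the site also brings the second intervention. A participant in Group 1 or 3 with no visits cannot have completed and so gets no sampler; one who completes does. The null hypothesis actually tested is therefore that neither web exposure nor the sampler affects use.

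This link comes from the design. It is separate from the familiar problem that motivated people visit more, and it would arise even if visiting were unrelated to motivation.

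At stake is interpretation. If Hypothesis 2 is right, a positive visits coefficient may appear for both sites although extra web exposure does nothing. The protocol would then read a sampler effect as evidence about the web sites.

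**Working it through.** **Inputs from the section on analysis and sample size**
- Two-sided 5% level: "based on comparisons between conditions with alpha of .05 two tailed".
- Effect and spread: "changes of 13% in percent time use between conditions with a standard deviation of .3", that is 13 and 30 percentage points.
- Group size: "A sample size of 85 per group is needed to have 80% power to detect an effect size d = .43".

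**The plan's own figure.** n = 2(1.960 + 0.842)²/0.43² = 84.9, so 85 per group. Allowing for 40% loss, 425/0.60 = 708.3, so 709. Both reproduce.

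**Assumptions, because the documents give no figures.** Completion p between 60% and 95%, occurring at the first visit. Completers make 1 + Poisson(0.5 or 1) visits and non-completers none. The web effect is zero, and visiting is unrelated to motivation. One post-test is analysed by linear regression. Each web format has 85 + 85 = 170 participants.

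**Step 1: the spurious effect.** Let non-completers have mean m in both groups. Among completers, half (the sampler group) have mean m + 13 and half have mean m. The expected contrast of 1 or more versus 0 visits is 13/2 = 6.5 points with no web effect.

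**Step 2: rejection rate for 0 versus 1 or more visits.** SE = 30·√(1/(170p) + 1/(170(1−p))) and z = 6.5/SE. The approximate rejection rate is Φ(z − 1.96) + Φ(−z − 1.96).

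| Completion p | SE | z | Rejection (approx.) |
|---|---|---|---|
| 60% | 4.70 | 1.38 | 28% |
| 75% | 5.31 | 1.22 | 23% |
| 85% | 6.44 | 1.01 | 17% |
| 95% | 10.56 | 0.62 | 9% |

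Simulation gives about 16–26% over 60–85% completion. The formula runs a point or two higher because it ignores the extra spread that the sampler creates among completers.

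**Step 3: other codings and inputs (simulation).** Simulation error and the assumed number of repeat visits move these figures by a point or two.
- Visit count, 60–85% completion: about 10–19%.
- Cut at 2 or more visits, 75–85% completion: about 6–9%.
- 95% completion, across codings: about 5–9%.
- Everyone completes at the first visit, 1 versus 2 or more visits: near 5%.
- Sampler effect halved to 6.5 points, 0 versus 1 or more visits, 10–40% non-completers: 7–11%.
- No sampler effect: near 5%.
- 142 per group (709/5, nobody lost), 13 points, 0 versus 1 or more visits, 10–40% non-completers: 19–42%.

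**Step 4: which adjustment works (0 versus 1 or more visits, 10–40% non-completers, 85 per group).**
- Covariate for assigned sampler arm: 14–27%. It shifts the arm means only. The contrast is still 13 points within the sampler group and 0 within the other, averaging 6.5.
- Covariate for actual receipt: 4.2–5.3%.
- Group 2 or Group 4 alone: 4.7–5.2%.

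**The case against.** - **The trigger is completion, not visit frequency.** A completer with one visit and a completer with ten both get the sampler. This stands. The distortion comes only from analysed non-completers in Groups 1 and 3, and it shrinks towards nothing as completion approaches 100% or if the cut lies well above the completing visit. A reader might infer that frequent visitors in general have the sampler and infrequent ones do not, or that the error rate is about 26% whatever happens. The documents support neither, since they give no completion rate, visit distribution or cut-point.
- **Pooling is inferred.** An article need not set out the full model, and the Data analysis plan carries a factor for being sent HPDs in both designs. That is fair. But web format is the only split stated for Hypothesis 3, and if that factor means the assigned arm, Step 4 shows that it does not help.
- **The test is admittedly underpowered.** This limits the consequence but does not remove it, because the protocol intends to interpret the result either way.
- **The percentages are not the plan's error rates.** They come from a regression at one time point, not the three-time mixed model. This stands; they show the mechanism and its rough scale.

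A reader might also infer that the pooled test must be dropped, or that Groups 2 and 4 alone would give a clean web-dose effect. Neither follows. Modelling receipt restores about 5% with everyone kept. In Groups 2 and 4 participants still choose how often to visit, as the section on the Interactive Web Intervention says, and the 5% there rests on assuming that visiting is unrelated to motivation.

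**Conclusion.** The point holds in a limited form. As written, the Hypothesis 3 test cannot separate web exposure from sampler receipt, and the assigned arm as a covariate does not cure this. Under the plan's own effect, SD and group size, with no web effect, the distortion runs from substantial to negligible: about 16–26% rejection for 0 versus 1 or more visits at 60–85% completion, and about 5–9% at 95%. Where the trial falls in that range depends on completion and coding, which the documents leave open, and on the sampler actually raising use.

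The consequence is confined to reading Hypothesis 3. Hypotheses 1, 2 and 4 and the sample size do not depend on it.

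**What to change.** Include actual sampler receipt (sent or not sent) as a covariate in the Hypothesis 3 model, entered in the same way as visits, including any interaction with time. The trial would know receipt because it mails the samplers. Keep all participants of each web format: the web-only group is what lets visits and receipt be told apart. Report the visits effect in Groups 2 and 4 alone as a check, and describe any visits effect as an association, not as proof of web dose.

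The cost is a change of analysis wording and some precision. For 0 versus 1 or more visits, the squared correlation between completion and receipt is (1−p)/(2−p), which is 0.286 at p = 60% and 0.130 at p = 85%. The standard error therefore grows by a factor of 1/√(1−0.286) = 1.18 or 1/√(1−0.130) = 1.07. Relying on the web-only group alone would cost √2 = 1.41. The plan already regards this test as underpowered.
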